## Interventions

### Explanation for the choice of comparators {6b}

We wish to observe the effect of video games on the rehabilitation of swallowing function. Therefore, the control group use the same components of the rehabilitation program without the video game effect. Both groups have the same duration of intervention.

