#### Intervention

The intervention was given once a day for 30 min per session, 5 times a week for 4 weeks. The experimental group received the video-game intervention and the control group received the conventional therapy intervention. Both groups received the usual care, including daily feeding education, position training, breathing control, improving cough technique, and thermal tactile stimulation. The researcher will participate in the patient's first three rehabilitation sessions to help guide the patient on rehabilitation methods, and the next 17 sessions will be done independently by the patient (Fig. 1).

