**Fig. 2 Fig2:**
[figure not shown]
Game contents and applications of the video-game based swallowing function training. Each game application targets a specific movement of the swallowing training. The target movements are represented by red arrows and circle

Game One—Lip Exercise: the game “Collecting Carrots” appears on the computer screen. Participants move the character in the game by drumming cheeks, left drumming cheeks, and right drumming cheeks, hold the movements for 2–3 s. After the character in the game moves to the left and right to reach the designated place, the carrot will automatically fall into the back basket of the character in the game, participants need to complete drumming cheeks, left drumming cheeks, and right drumming cheeks 15 times, respectively.

Game Two—Tongue Exercises: the “Maze Challenge” game appears on the computer screen. The participant uses tongue movements to make the characters in the game move. The participant extends the tongue, tongue up, tongue down, tongue left, tongue right, and the game character in the labyrinth is activated, up, down, left, and right by the participant's tongue movements. When the participant sticks out his tongue once and holds it for 3 s, the game character will move one space in the corresponding direction. The patient can rest for 2 s before proceeding. The route out of the maze was designed based on the route of the movement program of the patients’ tongue, and the game character walked out of the labyrinth when the patient completed the tongue movement. Each movement repeats 15 times.

Game Three – Lower Jaw Exercise: the “Little bird flying” game appears on the computer screen. In this game, participants control the direction of the bird's flight by lowering their jaw. Participants use their chin to press the rubber ball, hold it for 2–3 s, and then lift it up and the bird will fly down and around the obstacle. Participants are required to go around the obstacle a total of 15 times.

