The control group used the conventional swallowing function training. The lip exercise consisted of the following specific movements: opening mouth, closing mouth, drumming cheeks, left drumming cheeks, and right drumming cheeks; the tongue exercise consisted of the following specific movements: extending the tongue, tongue up, tongue down, tongue left, and tongue right. Each specific movement in the steps lasts 2-3 s, repeat 15 times and continue with the next movement. The lower jaw movement contains the following specific movements: keep the head as low as possible, and squeeze the rubber ball placed on the neck for 2–3 s, repeat 15 times.

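### The protocol says the arms share the same training components, but the control arm lists two lip movements that the game arm does not, so the contrast mixes the game effect with exercise content

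*Protocol article*

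**What the plan says.** Under Explanation for the choice of comparators {6b}, the protocol article gives observing the effect of video games as its purpose. It therefore states that "the control group use the same components of the rehabilitation program without the video game effect", and adds that "Both groups have the same duration of intervention".

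The exercises are set out in the Intervention text under Intervention description {11a}:

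- **Game arm, lip exercise:** "participants need to complete drumming cheeks, left drumming cheeks, and right drumming cheeks 15 times, respectively".
- **Control arm, lip exercise:** "opening mouth, closing mouth, drumming cheeks, left drumming cheeks, and right drumming cheeks", each repeated 15 times.
- **Tongue exercise:** the game arm lists five movements ("The participant extends the tongue, tongue up, tongue down, tongue left, tongue right"). The control arm lists the same five. Both use 15 repetitions of each.
- **Lower jaw exercise:** one movement with a rubber ball in each arm, 15 times.

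The schedule is given once for both arms: "The intervention was given once a day for 30 min per session, 5 times a week for 4 weeks".

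**The concern.** The comparator section makes a specific promise: take the game away and the remaining training is identical. If that were so, a difference between arms could be read as the effect of delivering the training through a game.

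The lists break the promise in one place. Controls train mouth opening and mouth closing, and no game is described as training either movement. Exercise content then differs between the arms in exactly the same way as the game does, so everyone without the game has the two extra movements and nobody with the game has them. No analysis can separate two factors that coincide completely with allocation.

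What is at stake is interpretation. Objectives {7} opens with the effect of the video game on swallowing function. If the lists stay as written, a positive, null or negative result describes two programmes that differ in delivery and in content, and the share due to the game is unknown.

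**Working it through.** The protocol states no figure that could be reproduced here. The check is a count of what each arm is told to do.

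**Inputs** (all from the Intervention text under {11a}): the movements listed for each arm and 15 repetitions per movement in both arms.

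**Formula:** repetitions per pass = number of movements × 15.

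| Exercise | Game: movements | Game: repetitions | Control: movements | Control: repetitions |
|---|---|---|---|---|
| Lip | 3 | 45 | 5 | 75 |
| Tongue | 5 | 75 | 5 | 75 |
| Lower jaw | 1 | 15 | 1 | 15 |
| Total | 9 | 135 | 11 | 165 |

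**Differences per pass**

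- Overall: 165 − 135 = 30 repetitions; 165/135 = 1.22, so control has 22% more.
- Lip only: 75 − 45 = 30; 75/45 = 1.67, so control has 67% more.
- Tongue and jaw: no difference in count. The lip exercise accounts for all of the excess.
- Share of a control pass spent on movements absent from the game arm: 30/165 = 18%.

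**Direction of any bias.** The number of passes per session is not stated, so two assumptions are set side by side.

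1. *One pass per session in each arm (assumption).* Both arms do 15 of every shared movement, and control does 30 repetitions on top. If the extra movements help, they would dilute an advantage of the game.
2. *The same total number of repetitions per session in each arm, spread evenly over the listed movements (assumption).* Each shared movement takes 1/9 = 11.1% of the work in the game arm and 1/11 = 9.1% in control. The ratio is 11/9 = 1.22, so the game arm does 22% more of each shared movement. If those movements matter more for the outcome than mouth opening and closing, this would favour the game arm.

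The two cases point in opposite directions. The documents neither choose between them nor give any figure for the effect of the two extra movements.

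**The case against.** **The word components can be read broadly.** Both arms have a lip, a tongue and a lower jaw exercise, the same five tongue movements, 15 repetitions of each movement, and the same session length, frequency and usual care. On that reading the sentence is true at the level of the three exercises. This stands as far as it goes and shows that the mismatch is narrow. It does not rescue the claim that only the game differs, because two movements occur in one arm alone.

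**The trial already compares programmes.** The hypothesis in Objectives {7} sets a video-game based intervention against conventional training. This stands: randomisation protects that comparison, and no test, sample size or control of bias fails because of the lists. What overreaches is the comparator statement and any conclusion about the game as such.

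**The article is condensed.** This does not remove the point. Both lists are given in the text with their repetitions, and they differ. The figure showing the game contents was not available, so the count rests on the text.

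**Stronger readings that the documents do not support**

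- *That timing differs materially between the arms.* Lip and jaw holds are 2–3 s in both. The game's tongue hold ("When the participant sticks out his tongue once and holds it for 3 s") lies within the control range of 2–3 s. The 2 s rest in that game is optional, and silence about rest in the control arm does not mean there is none.
- *That the jaw exercises differ.* The wording differs, but both press a rubber ball for 2–3 s, 15 times.
- *That repetition counts contradict the 30-minute session.* How the session is filled is operational detail that an article may leave to the full protocol.
- *That controls do 3,300 repetitions against 2,700 over the trial.* That is 165 × 20 and 135 × 20, which assumes one pass in each of 20 sessions. The protocol does not say so.
- *That the mismatch is bound to be conservative because the extra work is in the control arm.* That holds under the first assumption in the working but not under the second.

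**Conclusion.** The contradiction is real and confined to the lip exercise: five movements in control and three in the game arm, against a statement that the components are the same. Per pass this is 165 versus 135 repetitions (+22%), all from lip work (75 versus 45). These figures rest only on the stated lists and on 15 repetitions per movement. They do not extend to a total for the trial, and the direction of any bias cannot be settled from the document.

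The contrast between the arms therefore mixes the game effect with a difference in exercise content. A reader might infer that the trial's comparison is invalid. It is not, because the randomised comparison of the video-game programme with the conventional programme remains sound. What the design cannot support as written is attributing a result to the game itself. This should be fixed, but it does not undermine the trial.

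**What to change.** Reconcile the comparator section {6b} with the descriptions of the game and control exercises under {11a} before recruitment. Either of two routes is enough:

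1. Give both arms the same list of movements, with the set chosen by the clinical team. The statement in {6b} can then stand.
2. If the lists must differ, amend {6b} to say how and why. Limit the conclusion to the video-game programme versus the conventional programme, not the effect of the game itself.

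Which set of movements is right is a clinical question and is not judged here.

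The second route costs a few sentences. The first costs protocol text and possibly a small change to the exercise sheet or the game. Neither needs extra patients or staff. The Trial status section describes the trial as not yet recruiting, so on the protocol's own account the change can be made before anyone is treated under the unreconciled text.

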### Intervention description {11a}

#### Instrumentation

A video-game based swallowing exercise was developed by our team, consisting of a computer screen, and a facial recognition device. To ensure the patient-centered design of video-game, we adopted the TURF (Task, User, Performance, and Function) unified usability framework [19]. In TURF, usability refers to "the usefulness, usability, and satisfaction of the target user in achieving the goals of the work domain by performing certain sequences of tasks". This framework was developed for healthcare settings and is often the basis for ensuring good usability in design. Participants will face a computer and a facial recognition device, which is constructed from a facial landmark detector in the MediaPipe Artificial Intelligence model library. It will generate the 3D positions of 468 facial feature points on the facial images, including information about cheeks, mouth, chin and other facial areas [20]. Through changes in the 3D position of facial feature points, changes in facial muscles and expressions of participants will be detected, and the computer obtains biofeedback through real-time game-controlled computation.

#### Intervention

The intervention was given once a day for 30 min per session, 5 times a week for 4 weeks. The experimental group received the video-game intervention and the control group received the conventional therapy intervention. Both groups received the usual care, including daily feeding education, position training, breathing control, improving cough technique, and thermal tactile stimulation. The researcher will participate in the patient's first three rehabilitation sessions to help guide the patient on rehabilitation methods, and the next 17 sessions will be done independently by the patient (Fig. 1).

**Fig. 1 Fig1:**
[figure not shown]
Study flow chart and procedure

The experimental group used video-game equipment for swallowing function training. Participants in the experimental group were asked to sit on a chair, facing the computer screen, and complete the video-game training process. The video game rehabilitation training contains a total of three games (Fig. 2).

**Fig. 2 Fig2:**
[figure not shown]
Game contents and applications of the video-game based swallowing function training. Each game application targets a specific movement of the swallowing training. The target movements are represented by red arrows and circle

Game One—Lip Exercise: the game “Collecting Carrots” appears on the computer screen. Participants move the character in the game by drumming cheeks, left drumming cheeks, and right drumming cheeks, hold the movements for 2–3 s. After the character in the game moves to the left and right to reach the designated place, the carrot will automatically fall into the back basket of the character in the game, participants need to complete drumming cheeks, left drumming cheeks, and right drumming cheeks 15 times, respectively.

Game Two—Tongue Exercises: the “Maze Challenge” game appears on the computer screen. The participant uses tongue movements to make the characters in the game move. The participant extends the tongue, tongue up, tongue down, tongue left, tongue right, and the game character in the labyrinth is activated, up, down, left, and right by the participant's tongue movements. When the participant sticks out his tongue once and holds it for 3 s, the game character will move one space in the corresponding direction. The patient can rest for 2 s before proceeding. The route out of the maze was designed based on the route of the movement program of the patients’ tongue, and the game character walked out of the labyrinth when the patient completed the tongue movement. Each movement repeats 15 times.

Game Three – Lower Jaw Exercise: the “Little bird flying” game appears on the computer screen. In this game, participants control the direction of the bird's flight by lowering their jaw. Participants use their chin to press the rubber ball, hold it for 2–3 s, and then lift it up and the bird will fly down and around the obstacle. Participants are required to go around the obstacle a total of 15 times.

The control group used the conventional swallowing function training. The lip exercise consisted of the following specific movements: opening mouth, closing mouth, drumming cheeks, left drumming cheeks, and right drumming cheeks; the tongue exercise consisted of the following specific movements: extending the tongue, tongue up, tongue down, tongue left, and tongue right. Each specific movement in the steps lasts 2-3 s, repeat 15 times and continue with the next movement. The lower jaw movement contains the following specific movements: keep the head as low as possible, and squeeze the rubber ball placed on the neck for 2–3 s, repeat 15 times.

### Criteria for discontinuing or modifying allocated interventions {11b}

Neither the measurements nor the game manipulation produces any significant harmful side effects, as the game does not have graphic depictions of violence, and any of our measurements are not invasive. Therefore, we do not anticipate the need to modify the intervention during the study.

Patients can withdraw from the study at any time without adverse consequences for the patient. The investigator can also terminate a patient's participation in this study if the patient is uncooperative and/or does not attend the study visits. Patient data collected to date will be included in the analysis. If too much data is lost, the patient will be replaced by a new patient. The study will be terminated early in the event of serious adverse events, such as aspiration or vomiting.

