## Abstract

**Background:**

Dysphagia can lead to serious complications such as aspiration and aspiration pneumonia, timely and effective rehabilitation training can improve the swallowing function of patients. However, the conventional rehabilitation training methods used in clinical settings have shortcomings such as poor adherence of patients. We present the study design of a randomized controlled trial that evaluated whether video-game based swallowing rehabilitation training can effectively improve swallowing in patients with dysphagia and whether it has additional benefits compared with conventional training methods to improve swallowing function and training compliance among patients with dysphagia.

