### Strategies to improve adherence to interventions {11c}

Video-game based swallowing rehabilitation programs are safe with multiple game components, so high compliance with the program is expected. Adherence is based on the actual completion of the patient's swallowing function training. The actual completion of the dysphagia training by patients, including the number of training sessions completed and the duration of the training, is objectively recorded by the researcher. In addition to this, participants will be asked to complete a daily training diary in which they record the training activities they perform and record the duration, intensity, and symptoms of discomfort.

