Secondary outcomes in this study were quality of life, nutritional status, satisfaction and adherence. The swallowing quality of life (SWAL-QOL) questionnaire consists of 10 subscales and a symptom scale (14 items) to assess the severity of dysphagia symptoms. Scores range from 0 to 100, with lower scores indicating greater impairment of quality of life from dysphagia [24]. Body mass index (BMI) and Mini Nutritional Assessment Short Form (MNA-SF) were used to assess the nutritional status of the dysphagia patients. BMI is one of the most commonly used nutritional assessments among adults [25]. MNA-SF is commonly used to screen patients for malnutrition or risk of malnutrition with high sensitivity and specificity [26]. MNA-SF in combination with BMI showed higher accuracy [27]. The satisfaction questionnaire was designed based on the literatures. There are 15 items, involving 3 dimensions: training mode content setting, training mode format setting, and self-subjective feeling, and scored on a 5-point Likert scale. The higher the score, the more satisfied the patients were with the video-game training. Adherence was considered good if the patient could complete more than 80% of the training sessions of the corresponding training program; average if the patient could complete 50% to 80% of the training sessions; and poor if the patient could complete less than 50% of the training sessions. Patients are considered to have completed their training when they have completed more than 12 training sessions [28].

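### An unblinded investigator's undefined discretion to end participation, combined with replacement of patients, can cap or exchange poor adherers in the adherence outcome and conflicts with intention-to-treat

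*Protocol article*

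**What the plan says.** All references are to the protocol article.

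- **Ending participation ({11b}).** The investigator may end a patient's participation "if the patient is uncooperative and/or does not attend the study visits". The section gives no count of missed visits, no description of what counts as uncooperative, and no independent person who decides.
- **Data of such a patient ({11b}).** "Patient data collected to date will be included in the analysis". The next sentence reads: "If too much data is lost, the patient will be replaced by a new patient". No threshold is given.
- **Consent provisions ({26b}).** Data of a patient who withdraws consent are deleted. After discontinuation, keeping the data depends on the patient's authorisation.
- **Adherence as an outcome ({12}).** "Secondary outcomes in this study were quality of life, nutritional status, satisfaction and adherence". Above 80% of sessions is good, 50% to 80% is average, and the lowest category is "poor if the patient could complete less than 50% of the training sessions". More than 12 sessions counts as having completed training. Under {11c} the count is of training actually done, and the researcher records it.
- **Role in the trial's question (Abstract, Background).** The trial asks whether the game has added benefit "to improve swallowing function and training compliance among patients with dysphagia".
- **Blinding ({17a}, {17b}).** Only the outcome evaluator is blinded.
- **Analysis ({20a}, {20c}).** Intention-to-treat, with a per-protocol analysis for non-adherence.

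**The concern.** The person who may end participation knows the arm, and one of the two grounds is a matter of judgement about behaviour that can include not doing the training. Once participation ends during the four weeks, the session count stops. The adherence value then reflects both what the patient did and when the investigator acted. If the patient is also replaced, a poor adherer gives way to somebody else.

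At stake is the between-arm comparison of adherence, a secondary outcome and part of the stated question. The per-protocol set in {20c} depends on the same session counts. Replacement reaches further: exchanging randomised patients on the basis of what happened after randomisation undoes intention-to-treat for every outcome. A statistical analysis plan cannot repair this later, because it cannot recover sessions that never took place.

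**Working it through.** **1. Planned sessions.** {11a} gives 5 per week for 4 weeks: 5 × 4 = 20. The same section's split agrees: 3 guided + 17 independent = 20.

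**2. Categories in sessions, from the cut-offs in {12}.**
- Good: more than 0.80 × 20 = 16, so 17 to 20.
- Average: 0.50 × 20 = 10 up to 16.
- Poor: fewer than 10, so 0 to 9.
- Training completed: more than 12, so 13 or more.

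**3. Effect of ending participation after k sessions.** The count stays at k, and the remaining 20 − k sessions cannot be done.
- k of 9 or fewer forces poor.
- k of 12 or fewer forces not completed.
- k of 16 or fewer rules out good.

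Example: at k = 8, 12 sessions remained. Two more would have reached average (10), five more completed (13), and nine more good (17).

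**4. Weight of one patient.** 78 patients in two equal groups ({14}, {16a}) is 39 per arm, and 1/39 = 2.6 percentage points.

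**5. Illustrations. All patient counts here are assumed; the article gives none.**
- *Capping.* Four patients in one arm who would have been average are ended at 8 or 9 sessions. Poor goes from 8/39 = 20.5% to 12/39 = 30.8%, a shift of 4/39 = 10.3 points.
- *Replacement.* An arm has 29/39 = 74.4% good. Four poor adherers are replaced by patients who are good at the same rate: (29 + 4 × 29/39)/39 = 31.97/39 = 82.0%. Starting from 25/39 = 64.1%, the result is (25 + 4 × 25/39)/39 = 27.56/39 = 70.7%.
- *Loss from the denominator.* This could arise only where the {26b} authorisation is not given. Then 29/35 = 82.9% and 25/35 = 71.4%.

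Capping lowers an arm's adherence; replacement or loss raises it.

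**6. Do the grounds overlap with the outcome?** {12} and {18a} describe three assessment occasions: before training, after 4 weeks, and at follow-up. If these are the study visits, the first comes before allocation ({16c}) and the other two after training has ended, so missing one would not cut short the session count. Most sessions (17 of 20) are done independently. The overlap therefore rests on the uncooperative ground, which is undefined and wide enough to include not training.

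**7. {11b} against {20a}, {20c} and {26b}.** Intention-to-treat keeps every randomised patient in the assigned arm, whereas {11b} lets some be replaced. {11b} includes data to date without condition, whereas {26b} makes that depend on authorisation. As written, these statements cannot all be followed.

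**The case against.** The strongest reply is that {11b} itself says data collected to date are included, that {20a} and {20c} state intention-to-treat, and that a removed patient's session count is known and not lost. On that reading a poor adherer stays in the denominator with the sessions actually done. This stands, and it limits the denominator illustration to the case under {26b}. It answers neither the capping nor the replacement sentence.

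Three stronger readings are tempting, and the documents do not support them.
- *The ground for removal is the adherence outcome itself.* Study visits are not shown to be training sessions; only the cooperation ground can overlap.
- *The investigator can set the outcome's value.* For one patient the count can be frozen or capped but not raised, and sessions already done stand. An arm's rate can rise only through replacement or exclusion.
- *The plan favours the game.* The team developed it, and {11c} says "so high compliance with the program is expected", but nothing shows that the discretion would be used differently by arm. The illustrations pull in opposite directions.

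It is also fair that adherence is one of four secondary outcomes, that the hypothesis in {7} concerns swallowing function only, and that scoring detail can sit in an analysis plan. But the rules on ending participation and on replacement are stated in the protocol, so they have to be put right there.

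**Conclusion.** The point holds as a badly fixed rule. An investigator who is not blinded has undefined discretion to end trial participation on a ground that can overlap with adherence. Using it during training freezes that patient's count: 9 or fewer of 20 forces poor, and 16 or fewer rules out good. Replacement, also without a threshold, can exchange a poor adherer for another patient and contradicts intention-to-treat.

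The size and direction of any bias are unknown. With 39 per arm, four such decisions in one arm could move a category by about 10 points, but that rests on assumed counts and on all four falling in the same arm. No misuse is alleged. The conclusion assumes that the uncooperative ground may be applied to missed training, which the text allows but does not say.

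**What to change.** Reconcile {11b} with {12}, {20a}, {20c} and {26b}, separating the end of training from leaving the trial's follow-up and analysis:

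1. State that poor cooperation or missed visits do not by themselves remove a randomised patient from follow-up or analysis.
2. State that no randomised patient is replaced in the analysis.
3. Score adherence as sessions completed out of 20 for every randomised patient whose data may be used under {26b}, including those who stop early. Treat it as an observed value, not as missing or imputed.
4. Report participation ended by the investigator by arm, with reasons.

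Safety grounds and the patient's own withdrawal are unchanged, and nothing here says when training itself should stop.

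The cost is a few sentences in the protocol, some further contact with patients who attend poorly, and slightly lower reported adherence. The trial status section describes the trial as not yet recruiting, so on that version the change could be made before the first patient.
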